### Inclusion criteria

Inclusion criteria for midwifery students will be: studying at the seventh and eighth semester and willingness to participate in the study.

Inclusion criteria for service recipients (pregnant women) will be: age 18 – 40 years, Iranian nationality, singleton pregnancy, low risk pregnancy, and gestational age < 20 wks.

### Exclusion criteria

Exclusion criteria will be: history of psychiatric disorders, previous caesarean section, use of alcohol and tobacco, or having a disease that requires prenatal care by a specialist.

### Primary outcome

Clinical competence of midwifery students.

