**Methods:**

This sequential embedded mixed-methods study will include a quantitative and a qualitative phase. In the first stage, based on the Iranian midwifery curriculum and review of seminal midwifery texts, a questionnaire will be developed to assess midwifery students’ clinical competence. Then, in the second stage, the quantitative phase (randomized clinical trial) will be conducted to see the effect of continuity of care provided by students on maternal and neonatal outcomes. In the third stage, a qualitative study (conventional content analysis) will be carried out to investigate the students’ and mothers’ perception of continuity of care. Finally, the results of the quantitative and qualitative phases will be integrated.

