### Answer to the objects

A 1 to 4-point Likert scale will be used for scoring [29].

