### Sample size

According to the study objective and previous study results [32] with α = 0.01, β = 0.1, p_1_ = 0.51 and p_2_ = 0.021, the sample size will be *n* = 23. Considering a 20% dropout rate, the final sample size will be 58 women (29 women in each group).$$\begin{array}{l}n=\frac{{\left({z}_{1-\alpha /2}+{z}_{1-\beta }\right)}^{2}*\left[{p}_{1}\left(1-{p}_{1}\right)+{p}_{2}\left(1-{p}_{2}\right)\right]}{\left({p}_{1-}{p}_{2}\right)^{2}}\\ \mathrm{Z}_{1-\mathrm{\alpha }/2}=2.57\\ \begin{array}{l}\mathrm{Z}_{1-{\mathrm\upbeta} }=1.28\\ {\left(2.57+1.28\right)}^{2}*\left(0.55\left(0.45\right)+0.021\left(0.979\right)\right)/{\left(0.529\right)}^{2}=23\end{array}\end{array}$$

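### The sample size is a two-proportion calculation for an unnamed event, with the result counted in women, so the primary outcome, student competence, has no stated sample-size basis

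*Protocol article*

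**What the plan says.** The protocol article's Primary outcome section has one entry: "Clinical competence of midwifery students". Under the heading on answers to the questionnaire items it adds: "A 1 to 4-point Likert scale will be used for scoring". The Instruments and Follow-up sections have students complete this questionnaire at the start and at the end. Data analysis assigns the independent t-test to continuous data and lists ANCOVA to deal with confounding variables.

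The Sample size section works differently. It sets the error rates "with α = 0.01, β = 0.1", takes "p_1_ = 0.51 and p_2_ = 0.021" from a cited earlier study, and uses a formula for comparing two proportions. It reaches 23 per group, allows 20% dropout, and concludes that "the final sample size will be 58 women (29 women in each group"). It does not say which event the two proportions describe. The Data collection section then gives 58 students as well as 58 women, with no separate justification for the number of students. Mode of delivery, need for induction, admission to neonatal intensive care and other yes/no outcomes in women or newborns appear only under Secondary outcome.

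**The concern.** A statement of α and β describes one comparison: a given outcome, in given units, by a given test. Here the calculation and the primary outcome differ on each of these. The calculation concerns a proportion, expresses its result in women, and corresponds to a test of two proportions. The primary outcome is a questionnaire measure in students, for a t-test or ANCOVA. No planning quantity for competence enters the calculation.

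This matters because the trial's main conclusion will rest on competence. A reader who finds one sample-size paragraph and one primary outcome will naturally connect them and take the primary comparison to have 90% power. A non-significant competence result could then be given more weight as evidence of no effect than the design can justify.

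**Working it through.** **1. The plan's own figure.** The inputs from the Sample size section are z = 2.57 and 1.28, p2 = 0.021, and p1 = 0.51 in the text but 0.55 in the worked line. The printed formula is n = (2.57 + 1.28)² × [p1(1 − p1) + p2(1 − p2)] / (p1 − p2)².

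- With p1 = 0.51: 14.8225 × (0.2499 + 0.0206) / 0.489² = 16.8, so 17 per group.
- With p1 = 0.55: 14.8225 × (0.2475 + 0.0206) / 0.529² = 14.2, so 15 per group.

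Neither gives the stated 23. A continuity-corrected formula that the document does not print gives 23 with p1 = 0.55. The dropout step does reproduce: 23 / 0.8 = 28.75, so 29 per group and 58 in total. The mismatch in p1 and in the result is a separate error. Correcting it would still leave a calculation about a proportion.

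**2. Does any input describe competence?** The quantities used are two proportions, α, β and a dropout rate. Planning for competence would need an expected difference and an SD, or a cut-off that turns the score into a proportion. The document gives none of these.

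**3. What 29 v 29 can detect on competence.** Because no difference or SD is given, results are in SD units (d). For a two-sided t-test with n1 and n2 students, power comes from the noncentral t distribution with n1 + n2 − 2 degrees of freedom and noncentrality d × √(n1n2/(n1 + n2)). For 29 v 29 the multiplier is √14.5 = 3.808, with 56 degrees of freedom. Solving for 90% power gives d = 0.866 at α = 0.05 and d = 1.044 at α = 0.01.

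If competence is analysed by ANCOVA on its baseline value, the residual SD shrinks by √(1 − r²), where r is the pre-post correlation. The document gives no r, so 0.5 and 0.7 are assumptions:

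- r = 0.5: the factor is √0.75 = 0.866, so 0.866 × 0.866 = 0.75 SD and 1.044 × 0.866 = 0.90 SD.
- r = 0.7: the factor is √0.51 = 0.714, so 0.866 × 0.714 = 0.62 SD and 1.044 × 0.714 = 0.75 SD.

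| 29 v 29 students | Detectable at 90% power, α = 0.05 | Same, α = 0.01 | Power at an assumed 0.5 SD, α = 0.05 | Same, α = 0.01 |
|---|---|---|---|---|
| Unadjusted t-test | 0.87 SD | 1.04 SD | 47% | 23% |
| ANCOVA, r = 0.5 | 0.75 SD | 0.90 SD | 58% | 33% |
| ANCOVA, r = 0.7 | 0.62 SD | 0.75 SD | 75% | 51% |

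Giving up one degree of freedom for the covariate changes these powers by no more than about one percentage point.

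Both α values are shown because Sample size uses 0.01, while Data analysis reports 95% intervals and prints a significance threshold of 0.5. The level to be used for competence has to be settled before one column can be chosen.

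**4. Fewer students.** These two cases use an unadjusted t-test and rest on further premises. If the 20% dropout stated for women also applied to students (23 v 23), 90% power would need 0.98 SD (α = 0.05) or 1.18 SD (α = 0.01). The blocks listed under Randomization, five of 4 and three of 3, total 29 students: 10 + 6 = 16 intervention and 10 + 3 = 13 control. If only those were randomised, it would need 1.26 or 1.54 SD.

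**The case against.** The strongest reply is that the protocol never claims 90% power for competence. It prints β = 0.1 and does not tie it to any outcome. That is correct, and it narrows the criticism: there is no false power claim to withdraw, only a primary outcome without a sample-size basis.

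It can also be said that the event might itself relate to competence, since the calculation appeals to the study objective and to a source not available here, and the first specific objective is student competence. This cannot be excluded, but the section counts women, and no cut-off that would make competence a proportion is defined.

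Unadjusted t-test figures alone would overstate the difficulty, because a baseline score is collected and ANCOVA is listed. This stands in part. Data analysis does not name the baseline score as a covariate, so the adjusted rows above are conditional, but they belong in the range. The dropout and block-list cases also depend on premises the document does not state for 58 students, so they are not the main result.

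A reader might infer that the trial is underpowered for its primary outcome. The document does not support that. It gives no expected effect, and a true difference of about 0.9 to 1.0 SD or more could be enough with 29 per arm. The planned effect sizes and 95% intervals also give some protection against misreading a null result.

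Finally, sizing a trial on a secondary outcome can be legitimate, but that outcome must then be named and the resulting precision for the primary stated. Neither is done.

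**Conclusion.** The point holds in this form: the Sample size section supports a comparison of two proportions for an event it does not identify, and the primary comparison of student competence has no sample-size basis. The stated β = 0.1 is not a property of that comparison. This is visible in the printed calculation itself and does not depend on detail the article leaves out.

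For 29 v 29 students, the difference detectable with 90% power runs from about 0.62 to 0.87 SD at α = 0.05 and from about 0.75 to 1.04 SD at α = 0.01. The range depends on whether the baseline score is adjusted for and on an assumed correlation between 0.5 and 0.7. It assumes a two-sided test, equal SDs, independent students and no loss of students; with fewer students the detectable difference is larger. Whether any of these values is plausible for a new questionnaire cannot be judged from the document.

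**What to change.** Rewrite the Sample size section as follows.

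- Name the event behind p1 and p2, and say that the two-proportion calculation supports that outcome only.
- State that β = 0.1 does not refer to competence.
- Specify that competence is analysed by ANCOVA on the baseline score already collected. Give the detectable difference for the actual number of students per arm, at the α that the analysis will use, over a range of pre-post correlations.
- Convert that difference into questionnaire points using the SD from the 20-student pilot described under Reliability.

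The number of students per arm must first be reconciled between Data collection (58) and the block list under Randomization (29).

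The cost is a rewritten paragraph. Enrolment and data collection stay as they are, which matters because sampling for the quantitative phase is already in progress. The disadvantage is that the stated precision for the primary outcome will look less favourable than β = 0.1 suggests.

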### Secondary outcome

Mode of delivery, length of labor stages, the need to induction, postpartum bleeding first and fifth minute Apgar score, admission of neonate to the neonatal intensive care unit, breastfeeding initiation, and exclusive breastfeeding up to 6 weeks postpartum.

### Data analysis

Statistical analyses will be done using SPSS version 26.0 (SPSS, Inc., Chicago, IL, USA). The independent t-test and Chi-square tests will be used for continuous data and categorical data, respectively. ANCOVA test will be used to eliminate the influence of confounding variables. The effect size will be calculated. A 95% confidence interval (CI) and *p* values will be reported. *P*-values less than 0.5 will be considered statistically significant.

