### Data collection

This phase of the randomized clinical trial will be conducted with the participation of 58 undergraduate midwifery students at their 7th and 8th semesters. The students will be divided randomly to intervention (continuous care) and control (routine care) groups providing care to 58 pregnant women in six health centers and two hospitals (Sina and Razi) in Ahvaz city, southwest of Iran.

The study will begin after receiving the approval of the Ethics Committee of Ahvaz University of Medical Sciences and registering the study in the Iranian Registry for Randomized Clinical Trials. Inclusion criteria will be willingness to participate in the study.

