### Intervention

Women who meet the inclusion criteria will be recruited in the study using a non-probability convenience sampling method. Women in the intervention group will be included in the study after their first pregnancy visit (6–10 weeks of gestation) and will receive continuous care by midwifery students. Women in the control group will receive the usual and routine care, and will be included in the study at the time of delivery. They will have a gestational age of more than 37 weeks based on the inclusion criteria of the study. Their delivery will be performed by midwifery students who will follow them up until six weeks after delivery.

At first, the necessary training will be given by the lead researcher (FR) to the students in orientation sessions held for both groups separately. In the intervention group, each midwifery student as the main midwife will be responsible for taking care of two or three pregnant women and will be the back-up midwife for two other pregnant women (under the supervision of other students). The lead researcher will create a group in WhatsApp with the participation of students in the intervention group, and they can communicate with each other and the researcher. Also, the midwifery students will be directly and indirectly under the supervision of a qualified person (lead researcher). Another WhatsApp group will be created for the women of the intervention and control groups (to facilitate communication between the researcher and the women). Two midwifery students will be introduced to each pregnant woman in the intervention group (as a main midwife and a backup midwife). If the main midwife is not available, the woman will be in contact with the backup midwife. The backup student will meet the woman at least once and will be introduced to her.

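### For the maternal and neonatal secondary outcomes, the named tests ignore women sharing a student, and ANCOVA, the only named adjustment, does not suit the binary outcomes

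*Protocol article*

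**What the plan says.** The Data analysis section of the protocol article names two tests for group comparisons: "The independent t-test and Chi-square tests will be used for continuous data and categorical data, respectively". Its one sentence on adjustment is "ANCOVA test will be used to eliminate the influence of confounding variables". It names no method for clustered data and no regression for binary outcomes.

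The Intervention section says that in the intervention group "each midwifery student as the main midwife will be responsible for taking care of two or three pregnant women", and that each student is also back-up for two other women. It does not say how many women a control student looks after. The Data collection section describes the trial "with the participation of 58 undergraduate midwifery students at their 7th and 8th semesters", caring for 58 women.

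The Secondary outcome section begins "Mode of delivery, length of labor stages, the need to induction, postpartum bleeding" and goes on to the two Apgar scores, NICU admission, breastfeeding initiation and exclusive breastfeeding to six weeks. The Primary outcome section names the students' clinical competence.

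On how women reach an arm, the Randomization section ties the arm to the hospital of birth, one hospital per arm, and runs the control period first. The Intervention section describes convenience sampling, with intervention women entering after a first visit at 6–10 weeks and control women entering at delivery, beyond 37 weeks.

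**The concern.** The intervention works through one student's relationship with, and care of, a small group of women. Women who share a student may therefore resemble each other in outcomes such as length of labour or breastfeeding. The independent t-test and the chi-square test leave any such correlation out. If it is positive, standard errors are too small, intervals too narrow and p-values too low.

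The second problem is adjustment. Women are not individually randomised, the arms are two hospital populations, and entry into the study differs by arm, so baseline differences are to be expected. ANCOVA models a continuous outcome. Mode of delivery, induction, NICU admission, breastfeeding initiation and exclusive breastfeeding are naturally yes/no or two-category. For these the article names no suitable adjusted analysis, only a crude chi-square test.

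Pregnancy outcomes are one of the specific objectives and the sample size is expressed in women, so these comparisons will carry weight in the report.

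**Working it through.** **The plan's own figure.** The Sample size section uses "α = 0.01, β = 0.1" and "p_1_ = 0.51 and p_2_ = 0.021" and states 23 women per group. The printed formula gives (2.57 + 1.28)² × (0.51×0.49 + 0.021×0.979) / 0.489² = 16.8. With the 0.55 and 0.529 of the worked line it gives 14.2. A pooled-variance formula gives 22 with 0.51, and a continuity-corrected one gives 23 with 0.55. The dropout step holds: 23 / 0.8 = 28.75, so 29 per group and 58 in all. The mismatch in the 23 is a separate matter. What counts here is that the formula treats women as independent and has no term for clustering.

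**How many women per student?** The article gives three accounts.
- Data collection: 58 students for 58 women, or 58/58 = 1 woman per student and no clustering.
- Randomization: five blocks of 4 and three of 3, so 5×4 + 3×3 = 29 students, of whom 5×2 + 3×2 = 16 are intervention and 5×2 + 3×1 = 13 control. With 29 women per arm this is 29/16 = 1.8 and 29/13 = 2.2 women per student, about two.
- Intervention: two or three women per intervention student. With 16 students that needs 32 to 48 women, against the 29 planned.

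Two of the three accounts imply clustering at about two. They still do not agree with each other or with the first.

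**Effect on the tests.** Inputs: m = 2 (from the blocks) or m = 3 (upper end of the Intervention section). The intracluster correlation (ICC) is 0.05 to 0.20, which is my assumption. The nominal level is 5%, to match the 95% confidence intervals in the Data analysis section.
- Design effect: DE = 1 + (m − 1) × ICC.
- Variance inflation V of a difference between equal arms: V = DE if both arms are clustered, and V = (DE + 1)/2 if only the intervention arm is.
- True size (normal approximation): 2 × [1 − Φ(1.96/√V)].

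Example, m = 2, ICC = 0.20, both arms: DE = 1.20; 1.96/√1.20 = 1.789; size = 0.074.

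| m | ICC | DE | Size, both arms | Size, intervention arm only |
|---|---|---|---|---|
| 1 | any | 1.00 | 5.0% | 5.0% |
| 2 | 0.05 | 1.05 | 5.6% | 5.3% |
| 2 | 0.10 | 1.10 | 6.2% | 5.6% |
| 2 | 0.20 | 1.20 | 7.4% | 6.2% |
| 3 | 0.05 | 1.10 | 6.2% | 5.6% |
| 3 | 0.10 | 1.20 | 7.4% | 6.2% |
| 3 | 0.20 | 1.40 | 9.8% | 7.4% |

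In a clustered arm, 29 women carry the information of 29/1.05 = 27.6 to 29/1.20 = 24.2 independent women at m = 2, and 29/1.40 = 20.7 at the extreme.

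**Outcomes that ANCOVA does not fit.** Counting labour length as one outcome and the two Apgar scores as two, there are nine secondary outcomes. Five are binary, as listed above. Labour length can take ANCOVA, the Apgar scores are not binary, and the scale of postpartum bleeding is not fixed.

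**The case against.** The strongest objection is that the nesting may not exist. On the Data collection section there is one woman per student, a design effect of 1 and nothing to correct. This stands, and it makes the clustering half of the point conditional. It does not remove it, because the Intervention section states the care arrangement explicitly and the block counts agree with about two women per student.

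Four stronger readings are tempting, and the article does not support them.
- *All maternal and neonatal standard errors are too small.* That needs a positive within-student correlation for each outcome. The article gives none, and it may differ between, say, breastfeeding and Apgar score.
- *Tests run at nearly 10%.* The 9.8% needs three women for every student, clustering in both arms and an ICC of 0.20. The control cluster size is not stated.
- *The primary analysis is affected.* Competence is measured on the student, so women nested within students do not bear on it. A t-test or ANCOVA suits a score taken before and after.
- *The binary outcomes will be reported unadjusted.* The article does not say which outcomes ANCOVA covers, and an analysis plan not shown may add models. The article supports only this: the one method it names does not suit them. Five of nine is also a thin majority, and it would be lost if labour stages were counted separately.

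It is also fair to say that a better model has limits. Back-up duties mean that students are not clean, separate clusters. At the article's own p₂ of 0.021, about 29 × 0.021 = 0.6 events are expected in an arm, which no multi-covariate logistic model can use. And with one hospital per arm and the control period first, adjustment cannot isolate the effect of the care model.

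**Conclusion.** The point holds for the maternal and neonatal secondary outcomes only. The named tests assume independent women in a design that, on two of its three descriptions, gives students about two women each. The resulting error is modest: a nominal 5% test at about 5.6% to 7.4% with both arms clustered and about 5.3% to 6.2% with only the intervention arm clustered. With three women per student the upper figures are 9.8% and 7.4%. All of these rest on an assumed ICC of 0.05 to 0.20 and on the Intervention and Randomization sections, not the Data collection section, being right about students and women.

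The adjustment half needs no such assumption. ANCOVA is the only confounder control named, it does not suit the five binary outcomes, and the way women enter the arms makes confounding likely. This should be changed before analysis, but it does not threaten the primary outcome.

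**What to change.** 1. Reconcile the Data collection, Randomization and Intervention sections on the number of students and of women per student, and state the number for the control arm.
2. Analyse women's and newborns' outcomes with a GEE or mixed model clustered on the main student, with a small-sample correction: linear for continuous outcomes, logistic for binary ones.
3. Adjust for one or two prespecified baseline covariates that are already collected, such as parity and maternal age. With 29 women per arm, more is not supportable.
4. For rare outcomes, prespecify penalised or unadjusted exact estimates.
5. Keep the t-test or ANCOVA for the student competence score.
6. State that no adjustment can separate the effect of arm from that of hospital or period, so that the adjusted results are not over-read.

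The cost is analysis wording and no new data. Intervals widen slightly: at about two women per student with both arms clustered, by √1.05 to √1.20, or about 2.5% to 9.5%. If the reconciled design has one woman per student, the clustering term can be dropped and only the adjustment for binary outcomes remains to be fixed.

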### Randomization

To implement the intervention, the students will be divided into two intervention (providing continuous care for pregnant women) and control (providing standard care for pregnant women) groups. Allocating students will be done using permuted block randomization technique with a block size of four and an allocation ratio of 1:1. Five blocks of 4 pieces and 3 blocks of 3 pieces will be extracted randomly using WIN PEPI software. In each block of 4, 2 students will be in control and 2 will be in intervention group. Also, in each block of 3 students, 1 student will be in control and 2 will be in intervention group, and the arrangement of each person is random. To prevent contamination, first the control group will provide routine care, and then the intervention group will conduct continuity of care for pregnant women. Mothers are randomly selected based on the hospital where they will give birth. As a result, Razi Hospital will be the control group and Sina Hospital will be the intervention group.

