### Instruments

All students and pregnant women participating in this study will complete a demographic questionnaire. A checklist will be provided for collecting data during prenatal care, labor, and delivery.

Also, the midwifery students will complete the clinical competency questionnaire at the beginning and end of the study.

Care will be provided and recorded by the main student according to the pregnancy care protocol. Also, danger signs will be taught to the students according to the national protocol, and emergencies will be handled by the midwifery student under the supervision of the lead researcher. Admission to hospital will be arranged by the student, and all information will be recorded. Pregnancy, labour and delivery, postpartum, and newborn checklist will be completed. Students will complete a demographic and obstetric questionnaire that includes questions about age, education, occupation, gravidity, parity, abortions, live and dead children, last contraceptive method, intended and unintended pregnancies, last menstrual period (LMP), gestational age, date of birth, body mass index (BMI), previous pregnancy and childbirth records, high-risk behavior of the mother and father, current history of special care, test and ultrasound results, and participation in childbirth preparation class. Also, the following data will be recorded in the labor and delivery and post-partum checklist: checking the conditions of labor according to the partograph, length of labor, need for induction and the method used type of delivery, examination of perineal trauma, postpartum bleeding, and examination of the condition of the mother up to 6 weeks after delivery. In addition, the amount of bleeding will be checked visually and by measuring the level of hemoglobin and hematocrit. Apgar score of the newborn will be recorded (in infant checklist) in minutes 1 and 5. Also, the newborn’s hospitalization status, breastfeeding and anthropometric indices will be recorded.

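### Mode of delivery and induction are left to an unadjusted chi-square test, although nothing balances first and later births between the hospital groups and parity is recorded

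*Protocol article*

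**What the plan says.** All references are to the protocol article.

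- **Tests.** Data analysis: "The independent t-test and Chi-square tests will be used for continuous data and categorical data, respectively". The next sentence adds ANCOVA to deal with confounding. It names no covariate and does not say which outcomes ANCOVA applies to.
- **Outcomes.** Secondary outcome lists mode of delivery and need for induction (both binary or categorical) and length of the labor stages (continuous). The primary outcome, student competence, is measured on students and is not affected.
- **Eligibility.** Inclusion criteria require "age 18 – 40 years, Iranian nationality, singleton pregnancy, low risk pregnancy, and gestational age < 20 wks", with no limit on parity. Exclusion criteria include "history of psychiatric disorders, previous caesarean section, use of alcohol and tobacco".
- **Allocation.** Randomization covers the students: "Allocating students will be done using permuted block randomization technique with a block size of four and an allocation ratio of 1:1". For the women, "Razi Hospital will be the control group and Sina Hospital will be the intervention group". Under Intervention, women are "recruited in the study using a non-probability convenience sampling method".
- **Data held.** Instruments lists "age, education, occupation, gravidity, parity, abortions, live and dead children" among the recorded items, so parity is available for every woman.

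**The concern.** Eligibility admits first-time mothers, and it admits women with earlier births only if none of those births was a caesarean. The later-birth group is thus selected for past vaginal delivery, so a contrast in caesarean risk between the two groups is to be expected. Its size is not in the documents and is assumed below.

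The women's group is set by hospital, and recruitment within it is by convenience. No design step balances parity, and nothing confines an imbalance to what chance would give. A crude chi-square test then compares two arms whose parity mix may differ, and reads that difference as an effect of the care model or lets it cancel a real one.

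The article does intend to deal with confounding, but ANCOVA is a method for continuous outcomes. For mode of delivery and induction the stated intention has no stated method that can carry it out. Pregnancy outcomes are one of the specific objectives, and the Background motivates the trial partly by unnecessary caesareans, so the matter counts even for secondary outcomes.

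**Working it through.** **Inputs from the article.** 29 women per group (Sample size). It follows from the stated 23 and 20% dropout: 23 / 0.80 = 28.75, rounded up to 29. Whether the printed formula yields 23 is a separate question and does not enter here.

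**Assumptions.**
- Caesarean risk is 30%, 40% or 50% in first births and 5% or 10% in later births.
- There is no treatment effect.
- The test is an uncorrected chi-square test at two-sided 0.05, the level that matches the planned 95% confidence interval.

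**Step 1: how large an imbalance could chance alone give?** With half the women having a first birth, the standard error of the difference in shares is sqrt(2 × 0.25 / 29) = 0.131. The normal approximation gives P(difference ≥ 20 points) = 0.128. Exact binomial calculation for 40-60% first births gives:

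| Imbalance | Probability by chance |
|---|---|
| at least 20 points | 0.14-0.15 |
| at least 30 points | 0.022-0.025 |

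These describe random sampling. Allocation by hospital is not random sampling, so they are a reference and not an upper bound.

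**Step 2: the false difference.** Arm risk = share of first births × risk in first births + (1 − share) × risk in later births. The false difference is therefore imbalance × (risk in first births − risk in later births).

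- 20 points, smallest contrast: 0.20 × (0.30 − 0.10) = 0.04.
- 20 points, largest contrast: 0.20 × (0.50 − 0.05) = 0.09.
- 30 points, smallest contrast: 0.30 × 0.20 = 0.06.
- 30 points, largest contrast: 0.30 × 0.45 = 0.135.

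**Step 3: the false-positive rate.** Exact binomial rejection probabilities, 29 against 29, treating the parity shares as population proportions:

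| Risks, first / later | 60% v 40% first births: arm risks | Rejection | 70% v 40% first births: arm risks | Rejection |
|---|---|---|---|---|
| 30% / 10% | 0.220 v 0.180 | 0.064 | 0.240 v 0.180 | 0.082 |
| 30% / 5% | 0.200 v 0.150 | 0.078 | 0.225 v 0.150 | 0.109 |
| 40% / 10% | 0.280 v 0.220 | 0.079 | 0.310 v 0.220 | 0.116 |
| 40% / 5% | 0.260 v 0.190 | 0.093 | 0.295 v 0.190 | 0.148 |
| 50% / 10% | 0.340 v 0.260 | 0.097 | 0.380 v 0.260 | 0.156 |
| 50% / 5% | 0.320 v 0.230 | 0.115 | 0.365 v 0.230 | 0.195 |

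With equal shares (50% in each arm) the same calculation gives about 0.05.

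If the parity counts are fixed instead, rejection is about 0.05-0.06 at 17 v 12 first births (a 17-point imbalance) and 0.07-0.14 at 20 v 12 (28 points). The benchmark with balanced counts of 15 v 15 is 0.02-0.04. The rates are lower on this basis, but so is the benchmark.

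**Step 4: labor length if parity is left out of the ANCOVA.** With an assumed 2-4 h longer labor in first births, 17 v 12 first births shift the mean by 2 × 5/29 = 0.34 h to 4 × 5/29 = 0.69 h. This applies only if parity is not among the covariates.

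**Induction.** No separate figure is offered. The mechanism is the same, but the documents give no induction rates.

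**The case against.** The strongest reply is that the article does plan for confounding: ANCOVA comes directly after the sentence on the t-test and chi-square test, and a list of covariates may well sit in an analysis plan that is not shown. This stands for labor length. A reader might infer that labor length gets only a crude t-test, or that parity is recorded and then ignored. The article supports neither: adjustment is planned for continuous data, and parity is unspecified, not excluded. The reply does not reach mode of delivery and induction, where the article names its methods and the adjusting one does not fit.

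A second reply is that the clinical contrast comes from outside the documents. That is fair, and the risks are labelled as assumptions with a range. A reader might go further and say that first births carry nearly all the caesareans. That has no source here and does not follow even from the assumed risks: at 50% v 10% with 40% first births, they account for 0.20 / (0.20 + 0.06) = 77%.

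A third reply is that the larger figures need a 30-point imbalance, which chance produces only about 2% of the time. True, so those figures should not be called ordinary. The 20-point case is the one that chance readily gives, and its effect on the false-positive rate is modest. The 30-point case remains relevant because hospital allocation is not chance.

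Finally, parity adjustment leaves the larger confounding untouched. Each hospital is one arm, the control phase runs first, and control women enter at delivery while intervention women enter in early pregnancy. This also stands. It limits what the fix can achieve, but it is no reason to leave a recorded prognostic factor out. Parity before the index birth is the same whether noted early or late in pregnancy, so the different entry times do not spoil it as a covariate.

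**Conclusion.** The point holds for mode of delivery and need for induction: the stated test is unadjusted, the stated adjustment method does not suit binary outcomes, and the women's allocation does nothing to balance parity. For labor length the point is only that parity should be named in the ANCOVA already planned.

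The size rests on assumed caesarean risks, no treatment effect, a 0.05 threshold and parity shares treated as population proportions. On that basis the false-positive rate is about 6-12% at a 20-point imbalance and about 8-20% at 30 points, somewhat lower with fixed parity counts. The bias can run in either direction. The affected outcomes are secondary, so this is a change worth making and not a threat to the primary analysis.

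**What to change.** In Data analysis:

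1. Replace the crude chi-square test for mode of delivery and need for induction with a parity-adjusted analysis (first v later birth): a Mantel-Haenszel risk difference, or logistic regression with a penalised fit if cells are sparse.
2. Name parity as a factor in the ANCOVA for labor length.
3. State that parity adjustment does not remove confounding by hospital, calendar period or time of entry, and limit the conclusions on women's outcomes accordingly.

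Where recruitment still allows, aim for a similar share of first births in both groups. This is secondary, because Study status says sampling is already in progress. A share set in early pregnancy may also shift by delivery under the 20% dropout allowed for, and some eligible women might be passed over.

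**Cost.** A few lines of text and no new data. The drawback is imprecision: with about half of 29 women in the later-birth stratum and an assumed risk of 5-10%, 14.5 × 0.05 to 14.5 × 0.10 gives roughly 0.7 to 1.5 expected caesareans per arm there. Estimates within that stratum will be weak, and only the combined parity-adjusted estimate should be interpreted.
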